# Effects of workplace upper extremity resistance exercises on function and symptoms of workers at a tertiary hospital: a randomized controlled trial protocol

**DOI:** 10.1186/s12891-022-05059-5

**Published:** 2022-02-05

**Keywords:** Clinical trial, Strengthening exercise, Upper extremity, Prevention, Musculoskeletal pain, Health promotion, Ergonomics

## Abstract

**Background:**

Work-related musculoskeletal disorders (WRMDs) are often caused by inadequate use of the musculoskeletal system during work. Evidence suggests that multimodal intervention through exercises, massage, education, and ergonomic guidelines reduces pain and symptoms in the neck and upper extremities and help to prevent musculoskeletal disorders. The purpose of this study will be to assess the additive effectiveness of a specific and individualized workplace strengthening exercise program to an ergonomic guidance in reducing fatigue, pain and discomfort in the upper extremities and neck perceived by workers.

**Methods:**

This trial was designed according to the Consolidated Standards of Reporting Trials - CONSORT guidelines. Participants will be employees of a tertiary hospital, with any complaints of pain or discomfort in the upper extremities during the past 12 months, without clinical musculoskeletal diagnosis. 166 participants will be randomized into parallels groups as control and workplace exercises. The primary outcomes will be Numerical Pain Scale, isokinetic muscle strength of abduction and isometric handgrip strength. Secondary outcomes on discomfort, fatigue, work capacity and dysfunction will be assessed by QuickDASH, Patient Specific Functional Scale, Neck Disability Index, Need for recovery, Work Ability Index self-report questionnaires and FIT-HANSA performance test. The Ergonomic Work Analysis will be done by Quick Expose Check, RULA, REBA, RARME, ROSA and HARM risk assessment ergonomic tools. We will analyze the difference between baseline and 12 weeks of intervention by T test of independent samples (95% confidence interval, *p* < 0.05). Clinical significance will be analyzed by the minimum clinically important difference and effect size by Cohen index. The association between the variables will be analyzed by construct validity with the hypothesis of correlations between pain and muscle strength, strength and functionality and strength and fatigue.

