To achieve more effective results with the implementation of workplace exercises, specific programs must be developed based on the objectives to be achieved. Some factors that are determinants of muscle performance must be taken into consideration, such as strength, power and endurance, together with the physiological adaptations to the exercises, which are influenced by intensity, exercise loads, volume, frequency and duration [22]. The resistance training is an effective method in the prevention and management of various disorders without distinction of sex. It is grounded on short term (6–8 weeks) mechanisms of neuromuscular adaptations, followed by gradual and posterior hypertrophy in the later phases (12–26 weeks) [23], leading to a balance and meeting individual’s needs and goals.

Recent studies aiming to evaluate the effectiveness of a physical exercise program performed in the workplace in reducing symptoms in the upper extremity and neck have shown promising results [1, 2, 4, 24–29]. Some randomized clinical trials have observed a reduction in pain and symptoms in the neck and upper extremity after the application of a multimodal intervention protocol composed by specific resistance exercises, muscle stretching, massage, educational and ergonomic guidelines within the work environment [2, 4, 20, 27–29].

Considering the aforementioned about previous studies, the aim of this study is to assess the additive effectiveness of a specific and individualized workplace strengthening exercises program to a protocol of ergonomic guidance in reducing fatigue, pain and discomfort in the upper extremity and neck of workers in a university hospital. Our hypothesis is that the group submitted to resisted exercises will demonstrate a decrease in musculoskeletal complaints and a better functional performance, in comparison to the group receiving only ergonomic guidance.

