#### Workplace exercise group

In addition to the ergonomic guidance, the WEG group will attend exercise sections 3 times/week, for 12 weeks. Exercise sections will take place inside the hospital, according to the workers’ availability during the breaks within working hours and will last 20 min. They will be divided as follows:Five-minute warm-up movements (3 × 15 repetitions each);Ten minutes of specific resistance strengthening exercises (3 × 10 repetitions each);Five minutes of stretching and relaxing movements (3 × 30 seconds each).

Resistance strengthening exercises for cervical region and upper extremity will be performed with individually defined load and progression. The movements will be: flexion, abduction and shoulder elevation in the scapular plane; external shoulder rotation; “push up” on the wall; elbow flexion associated with pronation (concentric) and supination (eccentric) and manual grasping (Additional file 1: Appendix 1). Regarding the intervals between the movements, active recovery will be adopted to neutralize the effects of muscle fatigue. The criteria for interruption will be pain that incapacitates the execution of the movement, pain and /or discomfort or sensory alterations such as tingling and numbness.

Two physiotherapists with the collaboration of an undergraduate student will conduct the intervention. Sections will happen in small groups (Fig. 2), favoring social contact and integration among the employees, with the intention to improve the employee’s mood, as well as their adherence to the protocol.

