##### Primary outcome measures

Pain: assessed by the Numerical Pain Scale (NPS) [35].Mean isokinetic peak torque: workers will be submitted to the upper limb strength assessment in the isokinetic dynamometer Biodex System 4 Pro™, following all the calibration and use recommendations referred by the manufacturer in the manual “Biodex multi-joint system - pro setup/operation manual”. Based on Prentice and Voight (2003) [36], all movements will be performed at a speed of 60°/sec. The dynamometer positions will be based on the positioning guidance material, except for the scapular plane elevation that was adapted for this study, based on Kapandji (2000) [37]. The movement to be tested in isokinetic mode will be shoulder elevation in the plane of the scapula. The test will consist of 5 direct repetitions, with the volunteer being instructed to perform his maximum force during all repetitions, with an interval of 3 min between one segment and another [38]. Isokinetic tests will be done bilaterally to collect the parameters of the mean peak torque in Newton (N).Isometric palmar grip strength: will be measured by the JAMAR™ dynamometer, an instrument recommended by the American Society of Hand Therapists (ASHT) because of its reported reliability and validity [39].

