## Data analysis

### Sample size calculation

The a priori sample size calculation was performed by GraphPad Statemate™, with power of 80%, effect size of 0.5 and alpha level of 0.05, based on the Numeric Pain Rating Scale and the isokinetic scores of the mean peak torque of the abduction movement in the scapular plane [54]. Seventh five participants will be needed per group. A total of 166 participants with pain or discomfort complaints of upper extremity who meet the inclusion / exclusion criteria and consent to participate will be included in the study, considering 10% sample size loss and analysis per intent to treat [30, 55].

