### Statistical approach

An investigator will receive the encoded data and perform the statistical analysis entered into a database Excel spreadsheet. The Kolmogorov-Smirnov test will be used to verify the normality distribution of the data. Descriptive statistics (frequencies, means, standard deviation, confidence interval) will be used to analyze the sociodemographic characteristics of the participants. The significant statistical difference between the outcome groups will be analyzed by the T test of independent samples to compare the means at the baseline and after 12 weeks of intervention, using as outcome variables the numeric pain scale, the mean isokinetic scores of peak torque and work, the patient self-reported questionnaires, with 95% confidence interval, *p* < 0.05. Responsiveness values for interventions to changes in clinical significance will be defined to score the minimum clinically important difference [56]. The Cohen Index will be defined to calculate the effect size, considering 0.3 low, 0.5 moderate and 0.8 high effect [57]. The association between the variables will be analyzed through the construct validity by the hypothesis tests, which determine the convergent and discriminant validity [58, 59]. It is expected that there will be moderate inverse correlation between pain and muscle strength production, moderate correlation between strength production and functionality and strong to moderate correlation between strength production and fatigue endurance. The statistical program SPSS Statistics 20.0 will be used for all analyses [57, 60].

The confounding factors that could be accounted for in the statistical plan and potential to bias even with the randomization process are: occupations will be analyzed together for comparations between control and intervention groups, before and after the intervention but not in subgroups by level of activity load; and intention-to-treat analysis will be performed including data for the noncompliance volunteers, in exception for dropout cases due to loss of follow-up [61].

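### Three unranked primary outcomes share a plain 0.05 level with no success rule, and two measure strength in trained movements while the aim is symptoms and function

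*Protocol article*

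**What the plan says.** The abstract's Methods paragraph states: "The primary outcomes will be Numerical Pain Scale, isokinetic muscle strength of abduction and isometric handgrip strength". The section on primary outcome measures lists the same three constructs without ranking them. It specifies the isokinetic test as shoulder elevation in the scapular plane, done bilaterally, and the grip test as a JAMAR measurement.

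The abstract analyses the change from baseline to 12 weeks "by T test of independent samples (95% confidence interval, *p* < 0.05". The Statistical approach section repeats the level, "with 95% confidence interval, *p* < 0.05", and defines the comparison by "using as outcome variables the numeric pain scale, the mean isokinetic scores of peak torque and work, the patient self-reported questionnaires". Handgrip is not in that list.

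The sample size (80% power, effect size 0.5, alpha 0.05, 75 per group, 166 in total) is "based on the Numeric Pain Rating Scale and the isokinetic scores of the mean peak torque of the abduction movement", which covers two of the three primaries.

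The aim in the Background is an added effect of exercise in "reducing fatigue, pain and discomfort in the upper extremity and neck of workers". The hypothesis there names fewer musculoskeletal complaints and better functional performance. The exercise arm trains "flexion, abduction and shoulder elevation in the scapular plane" and also manual grasping. The control arm receives ergonomic guidance only.

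**The concern.** There are two linked problems.

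First, three co-equal primaries at 0.05 each need a rule saying whether one or all must succeed. Each choice breaks one of the stated design figures: any-of-three exceeds the 5% error level, and all-of-three falls short of 80% power. With no rule fixed in advance, the choice can be made after the results are known.

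Second, two of the three primaries are strength measures of movements that only the exercise arm trains. A between-group strength difference is the expected response to training and does not by itself show fewer complaints or better function. If any primary may carry the claim, the trial could be reported as positive while pain is unchanged.

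**Working it through.** **Inputs from the protocol article:** three primaries; t tests at p < 0.05 (taken as two-sided because of the 95% interval); effect size d = 0.5; 75 per group; 80% power; 10% loss.

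**Assumptions (not in the article):** in the main correlated case, pain–strength correlation 0.3 in the direction of benefit and torque–grip correlation 0.6. A common correlation ρ from 0 to 0.7 gives the range.

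**1. The plan's own figure.** With d = 0.5, alpha 0.05 two-sided and 80% power, the t test needs 64 per group (63.8 before rounding), not 75. With 75 per group, power for one outcome is 86%. The total follows from 75: 150/0.9 = 166.7, against 166 stated. The difference between 64 and 75 is a separate matter and errs towards more participants.

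**2. If any one primary suffices.** The chance of at least one false positive among k independent tests is 1 − 0.95^k.

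| Tests | Independent | Correlated |
|---|---|---|
| Two primaries listed under Statistical approach | 1 − 0.95² = 9.8% | – |
| Three primaries | 1 − 0.95³ = 14.3% | about 13% (0.3 and 0.6) |

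With a common ρ, the three-test figure is 13.7% at 0.3, 12.6% at 0.5 and 10.9% at 0.7.

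**3. If all three are required** (d = 0.5 on each, 75 per arm).
- Independent: 0.860³ = 64%.
- Correlations 0.3 and 0.6: about 70%.
- Common ρ = 0.7: about 75%.

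All are below 80%.

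**4. Chance of a strength-only positive under an any-one rule.** Suppose exercise has no effect on pain and the same effect d on both strength primaries, with 75 per arm. The probability that at least one strength primary is significant at 0.05 is:

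| Strength effect | ρ = 0 | ρ = 0.7 |
|---|---|---|
| d = 0.5 (the article's value) | 98% | 93% |
| d = 0.3 (assumed) | 70% | 58% |

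At d = 0.5, a Bonferroni level of 0.05/3 = 0.0167 lowers this only to 94% (ρ = 0) or 85% (ρ = 0.7). An adjustment alone therefore does not remove the mismatch with the aim.

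**5. Power under the repairs** (75 per arm, d = 0.5).
- Fixed sequence, pain first at 0.05: 86% for pain. The chance that pain and then torque both succeed is 0.860² = 74% if independent. For all three it is the 64–75% of step 3.
- Holm: the strictest step is 0.0167, where power is 74%. Later steps use larger levels, so 74% is a lower bound per outcome.

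**The case against.** The strongest reply is that this is a condensed article. A multiplicity rule is often left to an analysis plan, and a nominal p < 0.05 does not say that any single outcome wins. That is fair: a reader might infer that the authors have adopted an any-of-three rule, and the article does not say so. The point still stands, because the choice of primaries, the 0.05 level and the sample size are fixed here, and neither possible rule is compatible with both a 5% error rate and 80% power.

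Other points in the plan's favour:

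- **Number of tests.** A reader might count five by taking both sides for torque and for grip. The article documents bilateral testing only for the isokinetic measure and does not say that the sides are analysed separately. The five-test count is not supported.
- **Handgrip.** It is absent from the Statistical approach list, so the three-test figure depends on the abstract's general sentence. This is why 9.8% is shown beside 14.3%.
- **Role of strength.** A reader might conclude that strength is foreign to the trial. It is not. The abstract's Discussion refers to neuromuscular adaptation, and the analysis section expects strength to correlate with pain, functionality and fatigue endurance. Strength has a stated mechanistic role, but it is absent from the aim in the Background and from the hypothesis. The tests (dynamometry at 60°/sec, isometric grip) are also not the training exercises themselves, although the movements match.
- **The 75 per group.** A reader might take the excess over 64 as a hidden adjustment for two outcomes. The article states alpha 0.05, and at 0.025 the requirement would be 78 (77.3 before rounding), with 79% power at 75.

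**Conclusion.** The concern holds in this form: three unranked primaries are tied to an unadjusted 0.05 with no decision rule. An any-one reading gives 14.3% family-wise error if independent and about 13% under the assumed correlations. An all-three reading gives about 64% to 75% joint power in place of 80%. Because the two strength primaries test trained movements while the aim and hypothesis concern symptoms and function, a strength-only result could be presented as success without symptom benefit. With the article's own effect size on strength and none on pain, an any-one rule would give that result in 93–98% of trials.

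These figures rest on two-sided tests, 75 evaluable per arm, d = 0.5 where stated, and correlations that the article does not give. They do not show that the authors intend an any-one rule, or that strength should be removed from the trial.

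**What to change.** - **Order the primaries.** Test the Numerical Pain Scale at 12 weeks first at two-sided 0.05, then scapular-plane peak torque, then handgrip, stopping at the first non-significant result. Define each as one pre-specified value per participant; how the two sides are handled is for the authors to choose and state.
- **If the three stay co-equal,** use Holm and state the power (at least 74% per outcome at the strictest step, with 75 per arm and d = 0.5).
- **Under either option,** state that a strength-only result will not be reported as a symptom benefit.
- **Reconcile the analysis list** by adding handgrip under Statistical approach.
- **Keep the named secondary outcomes secondary.** They include the fatigue and function measures that the aim and hypothesis refer to.

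Cost: no additional participants. The text and the registry entry must be changed. Under the fixed sequence, strength alone can no longer carry the trial's claim, and the strength outcomes are formally tested only if pain succeeds.

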**Discussion:**

Although studies have shown promise outcomes for workplace exercises as an available therapeutic resource used to minimize complaints of pain and discomfort related to work, the results of this study aim to bring evidence about the benefit of a specific resistance exercise as an effective modality to facilitate mechanisms of neuromuscular adaptations, with gradual and posterior hypertrophy in the later phases.

**Trial registration:**

(NCT04047056, https://clinicaltrials.gov/ct2/show/NCT04047056?term=NCT04047056&draw=2&rank=1) on Dec 03, 2020.

**Supplementary Information:**

The online version contains supplementary material available at 10.1186/s12891-022-05059-5.

## Background

Work-related musculoskeletal disorders (WRMDs) are a group of functional and mechanical disorders, often caused by overuse or inadequate use of the musculoskeletal system during work [1–3]. Muscles, tendons, fascia, nerves, joint and bones can be affected, and the result is fatigue, decreased performance at the workplace, temporary disability and absenteeism with economic consequences [4]. WRMDs are the second major cause of sick pay benefits in social security [5] and its prevalence has been increasing [1].

The most affected areas by WRMDs are neck, upper extremity, and low back [6–8]. Neck and upper extremity disorders can be divided into specific conditions with clear pathology and diagnosis, such as carpal tunnel syndrome, or non-specific conditions, which are defined by the location of symptoms, with unknown or imprecise physiopathology, such as neck strain syndrome [9].

Risk factors at the workplace related to neck and upper extremity symptoms include physical factors (harmful postures, repetitive tasks and static contractions), organizational factors (excessive work and absence of breaks), and psychosocial factors [6, 9–12]. Many tools have been developed and validated for the work ergonomics assessment. They aim to facilitate the survey of data regarding the various demands and workplace setting, postures assumed during professional activities, the perception of the worker regarding symptoms and muscle fatigue, and also to identify and classify the risk factors for the development of WRMDs [13–15].

In order to reduce WRMDs many companies have been investing more in prevention programs with a multidisciplinary approach for the promotion and maintenance of health, providing safer working conditions [16–18], adequate ergonomics [19] and workplace exercises [1, 9, 20]. Workplace exercises consist of specific activities performed during the working time. They usually have a short duration, with both preventive and therapeutic approaches, avoiding overloading or leading the employee to fatigue. It is a physical activity based on exercises to compensate repetitive movements, the absence of movement, or uncomfortable postures assumed during the working period [21].

To achieve more effective results with the implementation of workplace exercises, specific programs must be developed based on the objectives to be achieved. Some factors that are determinants of muscle performance must be taken into consideration, such as strength, power and endurance, together with the physiological adaptations to the exercises, which are influenced by intensity, exercise loads, volume, frequency and duration [22]. The resistance training is an effective method in the prevention and management of various disorders without distinction of sex. It is grounded on short term (6–8 weeks) mechanisms of neuromuscular adaptations, followed by gradual and posterior hypertrophy in the later phases (12–26 weeks) [23], leading to a balance and meeting individual’s needs and goals.

Recent studies aiming to evaluate the effectiveness of a physical exercise program performed in the workplace in reducing symptoms in the upper extremity and neck have shown promising results [1, 2, 4, 24–29]. Some randomized clinical trials have observed a reduction in pain and symptoms in the neck and upper extremity after the application of a multimodal intervention protocol composed by specific resistance exercises, muscle stretching, massage, educational and ergonomic guidelines within the work environment [2, 4, 20, 27–29].

Considering the aforementioned about previous studies, the aim of this study is to assess the additive effectiveness of a specific and individualized workplace strengthening exercises program to a protocol of ergonomic guidance in reducing fatigue, pain and discomfort in the upper extremity and neck of workers in a university hospital. Our hypothesis is that the group submitted to resisted exercises will demonstrate a decrease in musculoskeletal complaints and a better functional performance, in comparison to the group receiving only ergonomic guidance.

## Methods

### Trial design

This will be a prospective randomized controlled trial with concealed allocation by using opaque, sealed envelopes consecutively numbered and included each group’s name and deviation from the intention-to-treat analysis [30]. The study was designed according to the Consolidated Standards of Reporting Trials - CONSORT guidelines [31] for randomized clinical trials and following the standard protocol items for randomized interventional trials (SPIRIT) [32]. Participants will be randomized to receive either ergonomic guidance alone or ergonomic guidance and workplace strengthening exercises (Fig. 1).

**Fig. 1 Fig1:**
[figure not shown]
Study description

The study follows all ethical considerations set out in the Declaration of Helsinki and has received the approval from the Local Research Ethical Committee CAAE: 02658018.2.0000.5440. It was prospectively registered at www.ClinicalTrials.gov (NCT04047056).

